### Exercise intervention

Participants in the Exercise group participate in the exercise program three times per week for 16 weeks for approximately 60 minutes per session, totaling 48 sessions. Participants train one-on-one with a Certified American College of Sports Medicine/American Cancer Society (ACSM/ACS) Cancer Exercise Trainer for each session. Aerobic exercise duration per session is increased by 5 minutes every 3-4 weeks resulting in a total of 45 minutes of aerobic exercise per session by week 16 of the intervention. The trainer documents attendance of each participant at each session. If sessions are missed, reasons are documented with make-up sessions allowable extending the program to a maximum of 18 weeks.

Sessions are comprised of machine- and free weight-based resistance exercise and aerobic exercise at the Clinical Exercise Research Center (CERC) in the Division of Biokinesiology and Physical Therapy at USC. Estimated one-repetition maximum (1-RM) and estimated VO_2_ maximum obtained during baseline testing is used to determine resistance load for each exercise and aerobic intensity, respectively. The exercise program (Table 2) complies with American College of Sports Medicine (ACSM) exercise guidelines for cancer survivors, which includes 20–60 minutes of aerobic exercise performed at least 3 times per week and 6–10 resistance exercises performed at least 1–3 days per week [41-43]. Participants are required to wear a Polar® heart monitor (Lake Success, NY) during each exercise session. Heart rate (HR) is monitored throughout the aerobic exercise sessions to maintain an exercise HR at 65-80% of maximum HR. This protocol is designed to include moderate-to-vigorous forms of activity, which are more beneficial in decreasing risk of mortality from breast cancer, cardiovascular disease and diabetes [30,31,44]. Aerobic exercise types include treadmill walking, jogging, hill walking, or stationary cycling. Each resistance exercise session includes the following exercises: 1) leg press; 2) lunges; 3) leg flexion; 4) leg extension; 5) chest press; 6) seated row; 7) biceps curls; and 8) triceps pushdown. Initial resistance is set at 80% of the estimated 1-repetition maximum (1-RM) for lower body exercises and 60% 1-RM for upper body exercises. When the participant is able to complete 3 sets of 10 repetitions at the set weight in 2 consecutive sessions then the weight is increased by 10%. Participants with a compression garment were required to wear the garment during the exercise sessions. Each daily session begins with a 5 minute warm up on the treadmill or cycle and 10 minutes of static stretching.

**Table 2 T2:** Combined exercise intervention

**Day 1**	**Day 2**	**Day 3**	**Day 4**	**Day 5**	**Day 6**	**Day 7**
Aerobic exercise: 30 minutes at 65-80% HR maximum; Resistance exercise: 3 sets of 10 repetitions, 45 second rest between sets	Rest	Aerobic exercise: 30 minutes at 65-80% HR maximum; No resistance exercise	Rest	Aerobic exercise: 30 minutes at 65-80% HR maximum; Resistance exercise: 3 sets of 10 repetitions, 45 second rest between sets	Rest	At-home aerobic exercise: 30 minutes at 65-80% HR maximum

### Follow-up period

After the 16-week intervention period has ended, participants in the Exercise group are asked to return to the CERC 12 weeks later to repeat the outcome measure testing. During the 12-week period, participants are encouraged to exercise on their own without study team supervision. This can be independent or group activity and participants may seek assistance from fitness professionals as they see fit. The participants are asked to maintain weekly physical activity logs and wear a pedometer on a daily basis during this period. The purpose of this follow-up period is to determine whether the participants remain active and can maintain the benefits gained from the exercise intervention.

### Outcome measures

The outcome measures tested in the study are summarized in Table 3.

**Table 3 T3:** Assessments and instruments used

**Outcomes**	**Instrument**	**T1**	**T2**	**T3**
**Primary endpoint**				
Components of MetS (5):		X	X	X
Biomarkers- Glucose, HDL, triglycerides	Analyzed in peripheral blood	X	X	X
Blood pressure	Pressure cuff under resting conditions	X	X	X
Waist circumference	Measuring tape	X	X	X
**Secondary endpoints**				
Cardiorespiratory fitness	4-minute walk test	X	X	X
Muscle strength	10-RM- leg extension, leg flexion, chest press, seated row	X	X	X
Body composition	DEXA, weight, height, lean mass, % body fat, hip circumference	X	X	X
Quality of life	SF-36, FACT-B, CES-D	X	X	X
Shoulder strength	Muscle force for SE and ER	X	X	X
Shoulder ROM	Measured with goniometer at 90° ER, forward flexion,	X	X	X
Upper limb musculoskeletal disorder assessment	DASH, PSS	X	X	X
Biomarkers- inflammation & endocrine function	Analyzed in peripheral blood	X	X	X
**Others**				
Breast cancer characteristics	Family history, TNM status, ER/PR status, HER-2 score	X		
Medical history	Recording of any pre-existing disease and allergies	X		
Treatment data	Pre-treatment: date and type of breast cancer, affected lymph nodes, chemotherapy type and dose, radiation- technique, type, dose, start/stop date, hormone therapy	X		

### Metabolic syndrome

The primary endpoint is change in the components of metabolic syndrome (MetS) from baseline to week 17. MetS is comprised of 5 components: hypertension, high waist circumference, hyperglycemia, low HDLs, and elevated triglycerides; an individual is diagnosed with MetS if they present with 3 out of the 5 components [45]. Therefore, at each time point, the 5 MetS components are assessed individually and each participant is given a score out of 5 based on the criteria used to determine whether each component lies within the normal range. The following criteria was used to score MetS: 1) blood pressure > 130/85; 2) waist circumference > 35 inches; 3) triglycerides ≥ 150 mg/dL; 4) HDL < 50 mg/dL; 5) glucose ≥ 100 mg/dL. Upon study completion, we will analyze changes in each component as well as the cumulative score.

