**Methods/Design:**

This study is a prospective randomized controlled trial (RCT) investigating the effects of a 16-week supervised progressive aerobic and resistance exercise training intervention on MetS in 100 breast cancer survivors. Main inclusion criteria are histologically-confirmed breast cancer stage I-III, completion of chemotherapy and/or radiation within 6 months prior to initiation of the study, sedentary, and free from musculoskeletal disorders. The primary endpoint is MetS; secondary endpoints include: muscle strength, shoulder function, cardiorespiratory fitness, body composition, bone mineral density, and QOL. Participants randomized to the Exercise group participate in 3 supervised weekly exercise sessions for 16 weeks. Participants randomized to the Control group are offered the same intervention after the 16-week period of observation.

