### Objectives

The primary objective of this trial is to determine the effects of a 16-week combined exercise intervention on components of metabolic syndrome (MetS) including waist circumference, blood pressure, fasting glucose, HDL, triglycerides, and glucose, compared to a usual care control group among breast cancer survivors. Secondary objectives are to determine the effects of exercise on cardiorespiratory fitness, muscle strength, body composition, quality of life, shoulder strength and range of motion (ROM), and serum levels of insulin, C-reactive protein, and glycosylated hemoglobin (HbA1c). Safety and feasibility of the supervised exercise program will be evaluated, and the sustainability of the effects will be assessed.

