### Sample size

The primary aim is to compare changes in overall MetS scores from baseline to week 17 between the Exercise and Control groups. Since MetS has not been investigated in breast cancer survivors at the time of project initiation, we chose to calculate sample size using changes in insulin following exercise in breast cancer survivors. This project is designed to detect a treatment effect based on insulin results with 80% statistical power at a 5% level of statistical significance. Ligibel et al. assessed insulin levels before and after a 16-week exercise intervention in breast cancer survivors [40]. Using their results, a sample size of 80 participants would detect a difference in mean insulin levels of 2.6 μU/ml assuming that the common standard deviation is 4.0 μU/ml using a two group t-test with two-sided 5% level of statistical significance. Therefore, to allow for a 20% maximum withdrawal rate, 100 participants will be recruited, of whom 50 will be premenopausal and 50 postmenopausal.

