### Data analysis

The main intervention effect will be assessed on the basis of a comparison between exercisers and controls as defined at randomization, regardless of exercise adherence, i.e., according to intent-to-treat principle. A 2 (group) × 2 (time) repeated measures analysis of variance (ANOVA) will be used to examine changes in MetS score and for each individual component of MetS. Stratification by type of therapy (i.e., surgery, chemotherapy, radiation) may result based on therapy regimens completed by enrolled subjects. Similar analyses as for MetS will also be performed for the secondary endpoints. Correlation analyses will be used to examine the relationship between changes of the various measured endpoints. Regression analyses regarding the repeated measurement design (T1, T2, T3) will be applied to investigate the association between exercise intervention, MetS, cardiopulmonary fitness, muscle strength, body composition, and the QOL dimensions. The influence of other potential confounding factors, such as age, clinicopathologic characteristics, and comorbidities will be explored and accounted for in the analysis. In addition, change in physical activity behavior post intervention will be explored for the follow-up time points using descriptive analysis.

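### The primary endpoint is the five MetS components in some sections and the overall 0–5 score in another, and nothing says which governs

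*Protocol article*

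**What the plan says.** The primary endpoint or aim appears in these places in the protocol article:

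- **Abstract, Methods/Design:** "The primary endpoint is MetS", without saying whether this means the diagnosis, the components or the score.
- **Objectives:** "The primary objective of this trial is to determine the effects of a 16-week combined exercise intervention on components of metabolic syndrome (MetS"), followed by a list of components in which glucose appears twice.
- **Table 3, Primary endpoint:** "Components of MetS (5"), with rows for the blood markers, blood pressure and waist. The score has no row.
- **Metabolic syndrome:** "The primary endpoint is change in the components of metabolic syndrome (MetS) from baseline to week 17". The section then defines a score from 0 to 5, one point per criterion met, and ends: "Upon study completion, we will analyze changes in each component as well as the cumulative score".
- **Sample size:** "The primary aim is to compare changes in overall MetS scores from baseline to week 17 between the Exercise and Control groups".
- **Data analysis:** a 2 (group) × 2 (time) repeated measures ANOVA "will be used to examine changes in MetS score and for each individual component of MetS". No order among these analyses and no significance level are given here.

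The only significance level in the article, two-sided 5%, is in the Sample size section, where it sizes the trial on insulin.

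**The concern.** Components and score are not two names for one quantity. Analysed as measured, a component registers any change. The score registers only crossings of a cut-off. The trial could show a clear effect on a component and none on the score, or the reverse. A reader of the final report could not tell from the protocol which result was meant to carry the primary conclusion, and the authors could cite a section for either.

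At stake is the error rate of that conclusion. A single declared comparison at 5% has a 5% false-positive risk. A choice among six analyses, made after the results are known, does not. Which endpoint is primary belongs in the protocol, and an analysis plan that picked one would still contradict other sections of this text.

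**Working it through.** **1. The plan's own figure.** Inputs from Sample size: insulin difference 2.6, SD 4.0, two-sided 5%, 80% power, 20% withdrawal. Equal allocation is assumed, as the ratio is not stated.

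- Normal approximation: n per arm = 2 × (1.96 + 0.84)² × (4.0/2.6)² ≈ 37.2, so 38 per arm, 76 in total.
- Two-sample t-test (noncentral t): 38.1, so 39 per arm, 78 in total. With 40 per arm the power is 81.9%.
- Withdrawal: 80 / (1 − 0.20) = 100.

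The stated 80 evaluable and 100 recruited are reproduced to within two participants. However, insulin is a secondary measure in the Objectives, so the calculation does not show whether the score or the components are primary.

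**2. Do the two endpoints differ?** The waist criterion is above 35 inches.

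- A fall from 40 to 37 inches is a 3-inch improvement in the component and changes the score by 0.
- A fall from 35.2 to 34.8 inches is a 0.4-inch change in the component and lowers the score by 1.

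The two endpoints can therefore give different answers.

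**3. Number of planned tests.** Data analysis names one for the score and five for the components, so six. No test of the 3-of-5 diagnosis is named. Blood pressure is one row in Table 3 and one criterion in the score, so it counts once.

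**4. False-positive risk if any one of six counts as success.** Each test is taken at an unadjusted two-sided 5%, borrowing the level from Sample size.

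- Independent tests: 1 − 0.95⁶ = 26.5%. For the five components alone: 1 − 0.95⁵ = 22.6%.
- Six equally correlated normal test statistics (400,000 draws): 22.6% at correlation 0.4 and 18.8% at 0.6.

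The score is built from the components, so it cannot be independent of them. A simulation of null trials allows for this: 40 per arm, five correlated components, the score derived from cut-offs, t-tests on change, 8,000 trials per setting. For two groups and two times, the t-test on change is equivalent to the group × time test in the planned ANOVA.

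| Between-component correlation | Any of five components or score below 5% |
|---|---|
| 0 | 25.4% |
| 0.2 | 24.4% |
| 0.4 | 21.4% |
| 0.6 | 18.0% |

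The simulation error is about √(0.25 × 0.75 / 8,000) ≈ 0.5 percentage points. The score tested alone gave 4.5% to 5.3% across the settings run, as expected for a single 5% test.

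Assumptions not in the article: the correlations, a baseline-to-follow-up correlation of 0.7, and shares of women meeting the five criteria of 40%, 80%, 35%, 45% and 40%.

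**5. Scale of the cost if the components stay primary.** A Bonferroni split over five gives 0.05/5 = 0.01 per test, which is also Holm's first step. On the insulin inputs (normal approximation), 0.01 needs 56 per arm: 112 evaluable, and 112/0.8 = 140 recruited. With 40 per arm the power is about 63%, against 82.8% at 5% by the same formula. Insulin is not a primary endpoint, so these figures show scale only.

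**The case against.** The strongest reply is that the Sample size section does name a single comparison, the overall score. On that reading the components describe the score, and the error is 5%. That reading is possible, but the article does not secure it. The Objectives, Table 3 and the Metabolic syndrome section, where objective and endpoint are formally set out, all say components, and nothing says which statement prevails.

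A second reply is that test order and adjustment are commonly left to the statistical analysis plan, which is not shown. This stands: the absence of an adjustment from the article is not the finding. The finding is the conflict between sections.

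Third, the Abstract's bare MetS is probably shorthand, since its Background states the aim in terms of components. This also stands. The firm conflict is two-way, components against score, and the Abstract is only unspecific.

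A reader might go further and infer that every version of the endpoint is tested at 5%, so that the false-positive risk is some 19% to 26%, or 30.2% (1 − 0.95⁷) with systolic and diastolic pressure counted separately. The document does not support this. Data analysis states no level, the 3-of-5 diagnosis has no planned test, blood pressure is one component, and no section says that any single significant result would count as success.

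**Conclusion.** The concern holds as an inconsistency. The primary endpoint is change in the five components in three places, change in the overall score in a fourth, and unspecified in the Abstract. The analysis section treats all six quantities alike. This needs correcting, because the primary conclusion is not tied to one endpoint.

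The size is conditional. The false-positive risk would be about 18% to 26% if any one of the six tests at an unadjusted two-sided 5% counted as success, for assumed between-component correlations of 0.6 down to 0. It would be 5% if the score alone is primary. The article fixes neither case, so the range shows what the ambiguity could cost. It is not the trial's error rate.

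**What to change.** Name one primary endpoint in the same words in the Abstract, Objectives, Table 3, Metabolic syndrome, Sample size and Data analysis sections. Two forms are acceptable:

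- **Score primary.** The between-arm difference in change of the overall MetS score from T1 to T2, tested at two-sided 5%, with the individual components secondary. This is the candidate the Sample size section already names.
- **Components primary.** Control the family-wise error across the five at 5%, for example with Holm, and make the score secondary.

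Make the change before the stored samples are assayed. The Biomarkers section puts the assays after the last participant has completed, so glucose, HDL and triglycerides, and with them the full score, are not available until then.

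The first form costs only wording. The second costs power, on the scale shown in the last step of the working. In both, a single significant component could no longer be called a primary success on its own unadjusted p-value. Neither form supplies a power basis for the chosen endpoint, because the sample size rests on insulin.

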#### Venipuncture

Fasting blood (~30 cc) is drawn from the antecubital vein by trained phlebotomists at the Clinical Exercise Research Center (CERC). Participants are asked to fast for 12 hours prior to the blood draw. Refreshments are provided following the blood draw and prior to proceeding with further testing.

#### Biomarkers

The Diabetes and Obesity Research Institute (DORI) at the USC performs appropriate standard assays to measure serum lipids (cholesterol, HDL-cholesterol, LDL-cholesterol, triglycerides), insulin, glucose, high sensitivity C-reactive protein (CRP), and glycosylated hemoglobin (HbA1c) from the peripheral blood samples. Fasting glucose, insulin, and HbA1c serve as metabolic biomarkers while CRP serves as an inflammatory biomarker [27]. Serum is derived from whole peripheral blood samples, processed within 2 hours after taking the blood sample and stored at −80° for analyses of biomarkers after completion of last study participant.

#### Waist circumference

A tape measure is used to obtain waist circumference measured at the midpoint between the lower margin of the last palpable rib and the top of the iliac crest. Hip circumference is measured, around the widest portion of the buttocks, with the tape parallel to the floor, to determine waist-hip ratio.

#### Blood pressure

The participant is asked to sit quietly for 5 minutes while resting her arm (ipsilateral to the affected breast) on a table so the brachial artery is level with the heart. A sphygmomanometer cuff is wrapped around the participant’s upper arm, just above the elbow and a stethoscope is placed on the hollow of the elbow so blood pressure can be measured.

### Physical fitness

All fitness measures are performed by trained study personnel at the CERC.

#### Cardiopulmonary fitness

A single-stage submaximal treadmill test is used to estimate maximal oxygen uptake [46]. Cardiopulmonary fitness testing is well established in cancer patients and recommendations for testing procedures as well as safety guidelines in clinical trials with cancer populations have been well defined [47]. The procedure is also used to exclude exercise-contraindicating cardiac impairments. Participants are instructed to walk so they are able to talk while walking at a speed of 2.0, 3.0, 4.0, or 4.5 mph on a treadmill (Desmo Woodway, Waukesha, WI) for 4 minutes at a 5% grade and heart rate is measured at the end of the test. Using HR, speed, age and gender, maximal oxygen uptake is calculated using the specific formula that applies to this test.

#### Muscle strength

Maximal voluntary strength is evaluated by the 10-repetition maximum (10-RM) method for the following exercises: chest press, latissimus pulldown, knee extension, knee flexion, (Tuff Stuff, Pomona, CA) which will be used to calculate 1-RM (maximum strength) values for the exercise intervention [48]. The study personnel demonstrate each exercise and then the participant is asked to complete 5 repetitions of a light weight to ensure proper form. The participant rests for 30 seconds and then is asked to lift a heavier weight 10 times. This is repeated until the participant is no longer able to complete 10 successful repetitions.

#### Body composition

BMI in kg/m^2^ is calculated from height and weight measurements obtained using a medical scale (Detecto® 437, Webb City, MO). Body composition (total lean mass and percent body fat) is measured from a whole body scan using Dual-Energy X-ray Absorptiometry (DXA, GE iDXA, Fairfield, Connecticut) and with bioelectrical impedance analysis (BIA, Biospace InBody 520, Cerritos, CA). The DXA is considered to be a valid and reliable reference method for body composition assessment [49]. BIA is a quick and non-invasive method, which determines electrical impedance, or opposition to the flow of an electric current through body tissues to calculate an estimate of total body water, fat-free mass and body fat [50]. We chose to include the DXA and BIA to assess ability to use more portable techniques such as BIA for future studies and to better determine possible differences between the two devices in this population.

### Shoulder health and lymphedema measures

#### Shoulder strength

Maximal muscle force produced by the primary agonist during scapular plane elevation (SE) and external rotation (ER of the upper extremity are measured using a hand held dynamometer (HHD; Hoggan Health Industries, Salt Lake City, UT). The participant sits in an armless chair with her back flush to the back of the chair, feet flat on the floor approximately shoulder width apart, and sitting with neutral posture. The participant is asked to push as hard as possible against the HHD for approximately 4 seconds. For each test (SE and ER), the dynamometer on the apparatus is aligned so that the resistance is in exactly the opposite direction of the direction of motion being resisted. Two trials are performed for each muscle test, taken sequentially. The subject is allowed to rest for 30 seconds between the two trials. The average of two trials is used for data analysis. Shoulder strength is regularly assessed in breast cancer survivors as a means to determine effects of surgery and treatment-related side effects [51] and is measured following our exercise intervention.

#### Shoulder active range of motion (AROM)

AROM is measured for shoulder forward flexion and shoulder ER at 90 degrees abduction.

